##### Data Analysis Plan

SPSS version 22.0 (IBM Corp) will be used for the analysis. The significance level will be set as *P*<.05. Numerical data will be presented using means and standard deviations, while categorical data will be presented using frequencies and percentages. Furthermore, a linear generalized estimating equation (GEE) will be used to estimate the parameters of a generalized linear model with a possible unmeasured correlation between observations from different timepoints for SBP and DBP (comparing pretest and posttest).

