##### Design

An RCT will be performed for the community-based program in 2 groups (with pretest and posttest) using the CONSORT (Consolidated Standards of Reporting Trials) guidelines. An RCT is preferred to reduce selection bias [23]. Participants in this study will be randomly allocated to either the control or intervention group. The control group will receive a standard health education intervention for managing hypertension, while the intervention group will receive the PBD formula. A single-blind technique will be used so that participants will be unaware if they are in the control or intervention group.

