##### Inclusion and Exclusion Criteria

The inclusion criteria are as follows: farmers aged 45-65 years with stage I hypertension (systolic blood pressure [SBP]: 140-159 mmHg and diastolic blood pressure [DBP]: 90-99 mmHg) according to the JNC VIII criteria, farmers performing appropriate work, and those providing a commitment to attend the study for 3 months. We will exclude those who have experienced stroke as they are not eligible for participation, those with hypertension of stage II or higher, those taking medications, and those who have been hospitalized.

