##### Outcome Measures

The main outcome measures in this study are SBP and DBP, which will be measured using a standard protocol employing a stethoscope and sphygmomanometer after stabilizing subjects for more than 10 minutes. Measurements of SBP and DBP (mmHg) will be categorized according to the JNC VIII criteria to determine hypertension for participants aged >18 years [24]. The length of work per day, time of rest during working, and hours of sleep per day will be assessed among the farmers. These factors will be measured as they can influence blood pressure among farmers, according to a previous study [2]. Manual blood pressure measurement is usually performed using a mercury device or a calibrated needle (aneroid). SBP and DBP are determined through auscultation by listening for the appearance and disappearance of Korotkoff sounds in the brachial artery. Blood pressure measurements will be taken after a 14-minute rest period, during which the researcher and the participant will have a conversation to reduce tension associated with the “white coat” effect. Measurements will be taken at the same time (ie, 8 AM before activities) with the same tool. Participants will be told not to wear clothes that are too thick. Blood pressure test results will be more accurate if the cuff is placed directly over the skin. Participants will be told to empty their bladder before measurement. For the measurement, participants will be told to sit with their arms on a table so that the elbows are in line with the heart, the back is well supported by the back of the chair, and the feet are on the floor.

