##### Data Collection Plan

At baseline, sociodemographic data, including age, gender, education level, smoking, hours of work, rest during working, and hours of sleep per day, will be obtained using a self-administered questionnaire. For measuring SBP and DBP at the PHC, participants will sit in a chair and relax for 10 minutes. Then, PHNs will measure blood pressure at least twice. If the blood pressure values obtained in the second measurement differ from the values in the first measurement by ≥10 mmHg, a third measurement will be carried out. The 2 measurement values with the smallest difference will be averaged to obtain the final value [24].

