##### Intervention

The intervention group will receive a PBD formulated by the researchers. Farmers will consume the plant-based food 3 times per week. For the PBD, we will adopt a standard protocol from previous studies [1]. Therefore, we have decided to provide the PBD for 6 months.

In the control group, participants will receive education on health and safety on attending the IHP for NCDs, and they will adopt healthy behaviors according to the health education. As they will receive health education, they will be able to lead a healthy life in the agricultural environment, with occupational health and safety.

In both study groups, health education will be provided before the program, which will include information on how to manage a healthy lifestyle while working as farmers, including diet, exercise, rest, and sleep, and how to address blood pressure problems among farmers. Participants will receive this health education in a single session for 60 minutes at the first screening meeting. All participants will receive a manual book on a healthy lifestyle in an agricultural setting.

The blood pressure of participants in both study groups will be maintained. If the blood pressure increases to hypertension stage II or above, appropriate treatment will be provided by the medical doctor in the PHC and the participant will be excluded from the study. Data will be obtained at registration and at the pretest and posttest assessments. For blood pressure data, we will use rounded values, with values ending in 0-4 being rounded to “0” and values ending in 6-10 being rounded to “10” (eg, 120-124 mmHg will be rounded to 120 mmHg, 125 mmHg will be used directly, and 126-130 mmHg will be rounded to 130 mmHg).

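### The trial's stated analysis compares pretest with posttest and names no between-arm contrast, so as written it does not test whether the diet works

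*Protocol article*

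**What the plan says.** The Design section sets up a two-arm randomised trial: "An RCT will be performed for the community-based program in 2 groups (with pretest and posttest"), and "Participants in this study will be randomly allocated to either the control or intervention group". The Introduction (third objective) and the Activity 3 Overview give its purpose as testing the effectiveness of the programme.

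Under Outcome Measures, "The main outcome measures in this study are SBP and DBP". The Data Analysis Plan says "The significance level will be set as *P*<.05" and gives one inferential method, a linear GEE accounting for "correlation between observations from different timepoints for SBP and DBP (comparing pretest and posttest"). The Abstract describes the same model by its time points, again without mentioning arm. Sample Size Determination uses the McNemar test, which is a paired test, and arrives at 96 participants.

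Three features of the design bear on a before-after comparison:

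- **Entry window.** The trial enrols "farmers aged 45-65 years with stage I hypertension (systolic blood pressure [SBP]: 140-159 mmHg and diastolic blood pressure [DBP]: 90-99 mmHg").
- **Shared education.** "In both study groups, health education will be provided before the program". The Intervention section places this single 60-minute session at the first screening meeting, and all participants also receive a manual.
- **Exclusion.** The Intervention section excludes from the study any participant, in either arm, whose pressure rises to stage II or above.

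**The concern.** Randomisation protects one comparison, that between the arms. A before-after change mixes any diet effect with everything else that moves blood pressure over the period. Here at least three such influences are built in: selection on a raised reading, education given to both arms, and removal of participants whose pressure goes up. All three push the observed change downwards.

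If the analysis is carried out as described, a significant fall could be reported as showing that the diet works when the control arm fell by as much. The Conclusion hopes that local government will adopt the intervention as policy, so the error would have consequences beyond the paper.

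A smaller point goes with this. Two main outcomes share one threshold, with no statement of how they combine into a single conclusion.

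**Working it through.** **1. The plan's own sample size.** Inputs from Sample Size Determination: odds ratio 2, 75% changing, alpha .05, power 80%. With 0.75 discordant and a ratio of 2, the two discordant proportions are 0.50 and 0.25, a difference of 0.25.

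n = (1.960 × √0.75 + 0.842 × √(0.75 − 0.25²))² / 0.25² = (1.697 + 0.698)² / 0.0625 = 91.8.

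With continuity correction: (91.8/4) × (1 + √(1 + 2/(91.8 × 0.25)))² = 95.75, so 96. The stated figure is therefore the two-sided, continuity-corrected McNemar number. The section also mentions one tail, but that would give 77. The sizing, like the analysis, rests on within-person change.

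**2. How far SBP falls with no effect at all.** Assumed, because the documents give no SDs: population mean SBP 135-140 mmHg, between-person SD 14, within-person SD 8-10, one reading per occasion. The entry window of 140-159 is from the protocol article. If the eligibility reading is also the pretest:

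expected fall = (1 − R) × (mean pretest of entrants − population mean), where R = 14² / (14² + within-person variance).

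- Smallest case (mean 140, within-person SD 8): R = 196/260 = 0.754; entrants average 148.8; fall = 0.246 × 8.8 = 2.2 mmHg.
- Largest case (mean 135, within-person SD 10): R = 196/296 = 0.662; entrants average 148.4; fall = 0.338 × 13.4 = 4.5 mmHg.

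If eligibility is set at a separate registration reading, pretest and posttest regress equally and the expected fall is about 0.

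**3. How often each test is significant with no diet effect.** Simulated at two-sided .05 with 48 per arm (96 split equally; the allocation ratio is not stated):

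| Situation | Within-arm pretest-posttest test | Between-arm test of change |
|---|---|---|
| Separate registration reading, no education effect | about 5% | about 5% |
| Eligibility reading is the pretest, no education effect | about 28-68% | about 5% |
| Eligibility reading is the pretest, education lowers SBP by 3 mmHg in both arms (assumed) | about 88-98% | about 5% |

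A wider set of assumptions (mean 130-140, between-person SD 15, within-person SD 5-10) moves the second row to 14-81% and the third to between 85% and over 99%. The between-arm column stays at 4.3-5.6%.

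A shared education effect is enough without any regression to the mean. With a separate registration reading and a 3 mmHg fall in both arms after the pretest, the SD of change is √2 × 8 = 11.3 to √2 × 10 = 14.1. The noncentrality is then 3/(11.3/√48) = 1.84 down to 3/(14.1/√48) = 1.47, and the within-arm test is significant in about 44% down to 30% of trials.

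**4. What 96 participants detect between arms.** With 48 per arm, 80% power and two-sided .05: (1.960 + 0.842) × √(2/48) = 0.57 SD. Adjusting for the pretest multiplies this by √(1 − r²); for an assumed r of 0.5 it becomes 0.57 × 0.866 = 0.50 SD.

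**5. Two outcomes.** If success on either SBP or DBP counted, the error would be 1 − 0.95² = 9.75% for independent outcomes, and 9.1% to 7.8% for correlations of 0.5 to 0.8.

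**The case against.** The bracketed phrase follows directly on the mention of time points. It may only name the two occasions rather than declare the sole hypothesis. A GEE in a two-group, pretest-posttest, CONSORT-reported trial would ordinarily carry an arm-by-time term, and a condensed article may leave model terms to a fuller plan. That reading is possible. However, nothing in the article supplies a between-arm comparison, and the McNemar sizing points the other way. The gap concerns which question is tested, not a detail of model specification.

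Several stronger inferences are not supported:

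- **That the plan makes a before-after test its primary analysis, or leaves the control arm out.** No analysis is called primary, and no within-arm test is declared.
- **That the false-positive rate is 30-70%.** This needs the eligibility reading to be the pretest. The Intervention section lists registration apart from the pretest, which would bring the rate from regression to the mean down to about 5%; the article does not settle which reading decides entry. Readings are also averaged: if the assumed within-person SD is reading-to-reading, averaging two lowers the fall to 1.2-2.7 mmHg and the rate to 18-47%. Part of the education effect could also precede the pretest.
- **That the error across SBP and DBP is 8-9%.** No either-outcome success rule is stated.
- **That the plan wrongly omits covariates.** Work, rest and sleep hours are measured at baseline, but the plan neither includes nor excludes them, and adding them is a matter of preference. Pretest pressure is already one of the modelled observations.

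**Conclusion.** The point holds in this form: the only inferential comparison stated for the trial is pretest with posttest, the sample size rests on the same kind of comparison, and no between-arm contrast is given. Followed as written, the analysis does not answer the effectiveness objective.

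That conclusion follows from the text and needs no assumed figures. How badly a before-after test would mislead does depend on assumptions: the SDs, 48 per arm, which reading decides eligibility, and whether education acts after the pretest. The range runs from about 5%, with a separate registration reading and no education effect, to about 30-70% from regression to the mean when the eligibility reading is the pretest, and higher with a shared education effect. The between-arm test holds near 5% in every case. The handling of SBP and DBP is secondary.

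**What to change.** In the Data Analysis Plan, state that effectiveness is tested by the between-arm difference in mean posttest SBP, adjusted for pretest SBP, or equivalently name the arm-by-time term of the GEE as that test. Label within-arm changes descriptive.

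Three consequences need attention, so this is slightly more than a wording change:

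- **Analysis population.** State who enters the comparison and reconcile this with the Intervention section, which excludes participants reaching stage II or above. An analysis of everyone randomised and that exclusion cannot both stand without explanation.
- **Sample size.** The McNemar figure does not carry over to a difference in means. Restate what 96 participants can detect: about 0.57 SD at 80% power with 48 per arm, before baseline adjustment. Say whether that is adequate.
- **Two outcomes.** Name SBP as primary, or test DBP only after SBP is significant. The cost is that DBP cannot be claimed alone.

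It would also help to say whether the eligibility reading is the pretest. No new data are needed, since both arms are already measured at pretest and posttest.

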**Methods:**

We will use the exploratory sequential mixed methods approach. There will be a qualitative study (phase I) in 2022 and a quantitative study (phase II) in 2023. We will analyze data using a thematic framework in phase I. In phase II, the study will involve (1) questionnaire development and validation; (2) examination of the prevalence of hypertension, the level of acceptability of a PBD, and the associated factors; and (3) a randomized controlled trial. We will recruit farmers with hypertension who meet the study criteria. Moreover, in phase II, we will invite expert nurses and nutritionists to assess the face and content validity of the questionnaire. We will use multiple logistic regression models to estimate the associated sociodemographic factors and the level of acceptability of a PBD. Furthermore, a linear generalized estimating equation will be used to estimate the parameters of a generalized linear model with a possible unmeasured correlation between observations from different time points for systolic and diastolic blood pressure.

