##### Sample Size Determination

The sample size will be determined using a traditional sample size calculation based on the McNemar test. The sample size in the McNemar test in this study should fulfill the following criteria: (1) directional hypothesis for 1 tail; (2) magnitude of expected change using the odds ratio (OR; OR=2); (3) alpha value of .05; and (4) required power of 0.8 or higher. The OR and the proportion are expected to change as a result of the intervention. Considering a 2-tailed approach, an effect size of 2.0 at an α value of .05 and power of 80%, and a change in 75% of the population as a result of the intervention, 96 participants would be needed to detect the effect.

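### The RCT plan states only a pretest-versus-posttest comparison and takes its 96 from a paired test; the intervention-versus-control contrast is nowhere named

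*Protocol article*

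**What the plan says.** The Design section of Activity 3 sets up two groups measured before and after: "An RCT will be performed for the community-based program in 2 groups (with pretest and posttest". It then says "Participants in this study will be randomly allocated to either the control or intervention group".

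The Data Analysis Plan names one inferential method for blood pressure, a linear GEE "for SBP and DBP (comparing pretest and posttest". The abstract's Methods paragraph describes the same model only by its "possible unmeasured correlation between observations from different time points for systolic and diastolic blood pressure". Neither place mentions an arm term, an arm-by-time term or a posttest comparison between arms.

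Sample Size Determination begins "The sample size will be determined using a traditional sample size calculation based on the McNemar test" and arrives at 96 participants.

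Three other statements affect what a before-after change means:

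- Entry is by a blood pressure window: "farmers aged 45-65 years with stage I hypertension", that is SBP 140-159 and DBP 90-99 mmHg (Inclusion and Exclusion Criteria).
- "In both study groups, health education will be provided before the program" (Intervention). This is a 60-minute session, and everyone also receives a manual.
- Participants whose pressure rises to stage II or above are treated and leave the study (Intervention). The same section lists registration, pretest and posttest as separate data points.

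**The concern.** A randomised control group is useful because it shares every cause of change over time except the one under test. Only the difference between arms isolates the diet. A time coefficient, or a change within the diet arm, also contains:

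- the effect of the education session and manual that both arms receive;
- the downward shift in the posttest mean when risers are taken out;
- regression to the mean, so far as the reading that admitted the farmer is also the pretest value.

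If effectiveness is judged on the stated contrast, a diet that does nothing can appear to lower blood pressure. Adjusting for baseline does not repair a test of time. The paired sample size points the same way, because it gives no power for a comparison between arms.

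**Working it through.** **1. The plan's own figure.** Inputs from Sample Size Determination: OR = 2, proportion changing pd = 0.75, α = .05 two-tailed, power 80%. The paired McNemar formula is

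n = [z_α(OR+1) + z_β√((OR+1)² − (OR−1)²·pd)]² / [(OR−1)²·pd]

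= [1.960×3 + 0.8416×√8.25]² / 0.75 = (5.880 + 2.417)² / 0.75 = 68.84/0.75 = 91.8.

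With continuity correction: (91.79/4)×[1 + √(1 + 2×3/(91.79×0.75))]² = 95.75, so 96. The stated number is reproduced, and nothing in it compares arms. The section also lists a "directional hypothesis for 1 tail"; a one-sided calculation gives 72 without the correction and 77 with it, so 96 matches only the two-tailed version. If the 96 are split equally and the paired test is run in one arm of 48, exact two-sided power is about 46%, against 79% for all 96.

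**2. False fall with no diet effect, qualifying reading used as pretest.** The documents give no SD or visit-to-visit correlation, so these are assumed: SBP normal, SD 15, 18 or 20 mmHg, correlation ρ from 0.6 to 0.9, and 1:1 allocation (48 per arm). The Introduction's 35.8% is taken as P(SBP ≥ 140). That figure is for hypertension in farmers generally, not for SBP alone or for ages 45-65. DBP was not modelled.

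- Population mean μ = 140 − 0.364×SD = 134.5, 133.5, 132.7.
- Mean excess over μ among those reading 140-159: E = SD×[φ(a) − φ(b)]/[Φ(b) − Φ(a)], with a = (140 − μ)/SD and b = (160 − μ)/SD. For SD 18: 18×(0.373 − 0.134)/(0.930 − 0.642) = 14.9. For SD 15 it is 13.4, and for SD 20 it is 15.9.
- Expected fall = (1 − ρ)×E. The chance of a significant fall is from the noncentral t with noncentrality fall/(SD of change/√n).

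For SD 18:

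| ρ | Fall (mmHg) | SD of change | Chance, n = 48 | Chance, n = 96 pooled |
|---|---|---|---|---|
| 0.6 | 6.0 | 14.6 | 80% | 98% |
| 0.7 | 4.5 | 13.0 | 65% | 92% |
| 0.8 | 3.0 | 10.9 | 46% | 76% |
| 0.9 | 1.5 | 7.9 | 25% | 45% |

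Over SD 15-20 the fall is 1.3-6.4 mmHg. The chance is 23-85% (n = 48) or 42-99% (n = 96), against a nominal 2.5% in that direction. Direct simulation at SD 18 agrees within about 2 points.

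**3. Separate pretest.** Pretest and posttest now both have expectation μ + ρE, so the expected change is 0 and the chance of a significant fall is 2.5%. If those at or above 160 at posttest are removed, the chance becomes 5-17% (n = 48) or 7-30% (n = 96). The education effect would add to this; the documents give no figure for it.

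**4. Arm-versus-arm test.** A second set of assumptions was also simulated: population mean 125-140, between-person SD 15, within-person SD 5-10 mmHg. The between-arm test of change rejected in 4.4-5.7% of trials (two-sided nominal 5%), with either pretest definition and with or without removal of risers, provided removal works alike in both arms.

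**5. What 96 offers for that contrast.** At 48 per arm, the difference detectable with 80% power is (1.960 + 0.8416)×SD×√(2/48):

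| Assumed SD of change (mmHg) | 8 | 10 | 12 | 15 |
|---|---|---|---|---|
| Detectable difference (mmHg) | 4.6 | 5.7 | 6.9 | 8.6 |
| Power for 5 mmHg | 86% | 69% | 53% | 37% |
| Per arm for 80% power at 5 mmHg | 41 | 63 | 91 | 142 |

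The 5 mmHg is illustrative; the protocol states no target difference.

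**The case against.** The strongest reply is that silence is being read as exclusion. The Data Analysis Plan lists no model terms at all. Its parenthesis follows a clause about correlation between timepoints and may only say which timepoints are meant. The trial is a two-arm CONSORT design with both arms defined, and a GEE on two arms at two times is a usual way to fit an arm-by-time term. A journal article may leave the term list to a fuller document.

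Much of this stands. A reader might infer that the control group plays no part in the analysis, and the documents do not establish that. A reader might also infer that a useless diet would usually be declared effective. That needs the qualifying reading to be the pretest, whereas the Intervention section lists registration separately. With a separate reading, regression to the mean contributes nothing in the model above. Even with the same reading, the chance at correlation 0.9 is only 23-29% for 48 in one arm. Averaging at least two readings per visit (Data Collection Plan) favours the higher correlations.

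The reply does not remove the point itself. The plan does not merely omit a term: it names a contrast, and that contrast is before versus after. The sample size separately rests on a paired test. Nothing written commits the analysis to the arm comparison, so a within-arm or pooled time effect could be reported as following the plan.

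**Conclusion.** The point holds as a fault in what is stated. The one contrast named for SBP and DBP is pretest versus posttest, the 96 is a paired number, and no between-arm comparison appears. The size of the resulting error is conditional. It ranges from a large inflation if the qualifying reading is the pretest, through a modest one if it is separate but risers drop out, to none from regression or removal if neither applies. All of these rest on assumed SDs and correlations. The shared education affects a before-after reading in every case, by an amount the documents do not allow to be calculated. The need to name the arm contrast does not depend on which case is true.

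**What to change.** In the Data Analysis Plan, replace the parenthesis with a statement such as: effectiveness is tested by the intervention-minus-control difference in SBP and DBP (arm-by-time coefficient in the GEE, or posttest difference between arms adjusted for pretest), with 95% CI; changes within each arm are descriptive.

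In Sample Size Determination, state that the 96 and its 80% power refer to a paired before-after test. Then give the power or detectable difference of 96 participants for the between-arm contrast, with the SD assumed.

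The analysis change costs a sentence and uses the same data and software. The sample-size change costs a short recalculation. Its drawback is that the restated power may be less favourable than 80%.
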